### 2.5. Sample Size and Power

Based on the mean standard deviation established for the VO_2peak_ in a previous study by Moholdt et al. (2009) [55] (SD = 4.75 mL/kg/min) and an estimated error (*d*) of 1.7, a valid sample size providing a 95% confidence interval (CI) comprise 30 patients in each group (*n* = *CI*^2^ × *d*^2^/*SD*^2^). Therefore, a final sample size of 30 for each group (a total sample size of 60 patients) will provide a power of 97% if between and within a variance of 1. Calculations to establish the sample size will be performed using RStudio 3.15.0 software (RStudio, Boston, MA, USA). The significance level will be set at *p* ≤ 0.05.

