Therefore, HRV is a biomarker that can indicate the health status of the cardiovascular system, serving as an effective tool for individualizing the training load in cardiac patients. Moreover, it can be used to measure cardiovascular responses to therapeutic interventions, with HIIT-based exercise being the most recommended option. However, with the goal of obtaining improved results regarding cardiovascular rehabilitation, it is still unclear whether to opt for HIIT training or to individualize HIIT training using HRV. We hypothesize that (i) both HIIT training and HRV-guided training will improve cardiorespiratory fitness, functional performance, heart rate variability, relative weight and fat distribution, inflammatory markers, cognitive function, and quality of life in post-stroke patients but that HRV-guided training will achieve better results; and (ii) HRV-guided training will be safer and more feasible and will generate more patient adherence to the program. The primary objective of the proposed protocol is to determine the effect of HIIT- compared to HRV-guided training on cardiorespiratory fitness in post-stroke patients who undertake an 8-week cardiac rehabilitation program. The secondary aims of this trial are (i) to determine the effect of HIIT training compared to HRV-guided training on heart rate variability scores in post-stroke patients, (ii) to investigate the effect of each exercise program in terms of the adaptations obtained in functional parameters, body composition, and the quality of life of these patients, (iii) to study the effect of both programs on inflammatory markers, (iv) to determine which exercise program is more effective at improving cognitive function, and (v) to analyze whether the two exercise programs are equally feasible and safe, as well as to evaluate their effect on patient adherence to the cardiac rehabilitation program.

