### 2.4. Outcomes

The primary outcome of this study will be the peak oxygen uptake (VO_2peak_) obtained in an incremental treadmill test. The secondary outcomes will be treadmill endothelial and work parameters; heart rate variability; functional parameters; relative weight and body fat distribution; quality of life; inflammatory markers; cognitive function; and exercise adherence, feasibility, and safety. The treadmill test and blood sample collection will be carried out by the cardiologist one week before and after the intervention. Data on functional performance, relative weight and body fat distribution, quality of life, and cognitive function will be recorded by the multidisciplinary group during the first and last weeks of the exercise intervention. Heart rate variability, exercise adherence, feasibility, and safety will be recorded daily during the intervention by the physical exercise graduate.

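### Section 2.5 prints its sample-size formula inverted, sizes one arm's mean instead of the arm difference, and states a 97% power that follows from none of its inputs

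*Protocol article*

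**What the plan says.** The primary outcome is VO2peak (section 2.4: "The primary outcome of this study will be the peak oxygen uptake"). The primary objective in the Introduction is a comparison of the two programmes: "to determine the effect of HIIT- compared to HRV-guided training on cardiorespiratory fitness in post-stroke patients". Section 2.8 plans an ANCOVA of the post-test value with baseline and age as covariates.

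Section 2.5 takes two numerical inputs, "SD = 4.75 mL/kg/min" from an earlier study and "an estimated error (*d*) of 1.7". It concludes that "a valid sample size providing a 95% confidence interval (CI) comprise 30 patients in each group" and prints the formula n = CI² × d² / SD². It then presents, as a consequence, that recruiting 30 per arm, 60 overall, "will provide a power of 97% if between and within a variance of 1". On the test level it says: "The significance level will be set at *p* ≤ 0.05". It does not say whether the test is one- or two-sided.

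The section names no difference between arms for which the power is claimed, and it does not connect the variance of 1 to the SD of 4.75.

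**The concern.** Section 2.5 is the only quantitative justification of the trial's size, and its parts do not fit together. The formula as printed cannot give 30. The method behind the 30 concerns how precisely one group's mean is estimated, while the trial's question is how far two groups differ. The power is expressed on a unit-variance scale that uses neither input.

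What is at stake is how the result will be read. Both arms receive active exercise and both are expected to improve, with HRV guidance expected to do better (Introduction). A trial described as having 97% power invites the conclusion that a non-significant VO2peak comparison shows HRV guidance adds nothing. That conclusion is sound only for differences as large as those the 97% actually refers to, and the reader is not told what they are.

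**Working it through.** **Inputs.** From section 2.5: SD = 4.75 mL/kg/min; d = 1.7 (no unit printed; taken as mL/kg/min, the unit of the SD); 95% confidence, so z = 1.96; 30 per arm; level 0.05. Assumed: two-sided test, no dropout, no clustering.

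**1. The plan's n.**
- As printed: 1.96² × 1.7² / 4.75² = 0.49.
- Inverted: 1.96² × 4.75² / 1.7² = 29.99, so 30.

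The figure of 30 is reproduced, but only by the reciprocal of the printed ratio.

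**2. What that n secures.** n = z² × SD² / d² is the number needed for a 95% CI of half-width d around a single mean. For the difference between two arms:
- Standard error = 4.75 × √(2/30) = 1.226.
- Half-width = 1.96 × 1.226 = 2.40 (2.45 with the t quantile on 58 df).
- A half-width of 1.7 for the difference would need 2 × 29.99 = 59.98, about 60 per arm.

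Under the planned ANCOVA the half-width shrinks by √(1 − r²), where r is the baseline to post-test correlation. The documents give no r. Assuming r = 0.5, it is 2.40 × 0.866 = 2.08; assuming r = 0.8, it is 2.40 × 0.6 = 1.44.

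**3. The plan's 97%.** Two-sample comparison, 30 per arm:

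| Reading | Power |
|---|---|
| Difference of 1 with SD 1 | 96.8% (exact t); 97.2% (normal) |
| Literal one-way ANOVA, between variance 1 and within variance 1 | 99.97% |

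The first reproduces the stated figure. On the plan's SD, a difference of 1 SD is 4.75 mL/kg/min, and 4.75 / 1.7 = 2.8 times the precision input. In the second, a variance of 1 between two means places them √2 = 1.41 SD apart, which is 1.41 × 4.75 = 6.7 mL/kg/min; it does not give 97% at 30 per arm. Neither reading uses 1.7.

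**4. What 30 per arm can detect, unadjusted, SD 4.75.** The difference detectable with 80% power is 3.49 mL/kg/min; with 97% power it is 4.79.

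**5. Illustration only: power if the arms differed by 1.7.** The standardised difference is 1.7 / 4.75 = 0.358.

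| Analysis | Assumed r | Power (exact t) |
|---|---|---|
| Unadjusted | none | 27.6% (28.3% normal) |
| ANCOVA | 0.5 | 35% |
| ANCOVA | 0.7 | 48% |
| ANCOVA | 0.8 | 62% |
| ANCOVA | 0.9 | 88% |

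The ANCOVA rows replace the SD by SD × √(1 − r²). Reaching 97% at 1.7 would need r of about 0.93.

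**The case against.** The strongest objection is that 1.7 is a precision input. Section 2.5 calls it an estimated error and uses it with a confidence level; nowhere is it a target, an expected effect or a minimum important difference. A reader might infer that the trial claims 97% power and really has 28%. The documents do not support that: they claim no power at 1.7, so the 28% contradicts nothing stated. It also describes an unadjusted comparison, whereas the planned ANCOVA could raise it to 88% at r = 0.9. This objection stands, and the figures at 1.7 are illustrative only.

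Second, a reader might take it as established that the 97% was computed for 4.75 mL/kg/min. The plan does not say so. The 1-SD reading is the one that fits at 30 per arm, but the wording is garbled, and the literal ANOVA gives 97.2% at 16 per group. The origin of the figure is therefore unknown. This also stands.

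Third, the inverted ratio alone is a printing slip: the right formula was evidently used, and no patient number changes. That is fair for the first point. It does not answer the second and third, because the correctly printed formula still concerns one mean and the power still rests on no stated difference.

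Nor is this detail left to a fuller document. The formula, the n and the power are all printed in the article, and they do not agree.

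**Conclusion.** Section 2.5 is wrong as written on three points. The formula is inverted (0.49 against 29.99). The 30 per arm comes from the precision of one arm's mean (±1.7), while the unadjusted precision of the primary comparison is about ±2.4. The 97% is presented as following from the preceding calculation but does not, and no between-arm difference accompanies it.

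The arithmetic on the first two points is certain given the plan's inputs. For the third, the missing link is certain and the 1-SD interpretation is an inference. The detectable difference of about 3.5 mL/kg/min at 80% power assumes SD 4.75, a two-sided 5% test, no covariate adjustment, no dropout and no clustering. ANCOVA would lower it by an amount that depends on a correlation the documents do not give. Dropout would raise it, as would any clustering: the Introduction calls the trial cluster-randomized, but no intracluster correlation or cluster size is available to quantify this.

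Whether 60 patients are too few cannot be decided from the documents, because no relevant between-arm difference is stated. The finding is that the stated power gives no basis for thinking they are enough.

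**What to change.** Rewrite section 2.5 and keep 60 patients:

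1. Print n = z² × SD² / d² and say that it gives ±1.7 mL/kg/min for one arm's mean.
2. State the between-arm precision: about ±2.4 mL/kg/min unadjusted, and the narrower ANCOVA value under a stated, justified baseline correlation.
3. Delete the 97%, or restate it as the power for a difference of 1 SD (4.75 mL/kg/min).
4. Give the difference detectable with 80% power (about 3.5 mL/kg/min unadjusted) beside the between-arm difference that the sponsor considers relevant, with its justification. The 1.7 should not become the target by default.
5. Say that these figures assume no dropout and no clustering, and revise them if allocation is by cluster.
6. State that the VO2peak result will be interpreted through the confidence interval of the arm difference.

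The cost is the wording of one section and a less favourable stated power. It adds no patients and leaves the planned analysis unchanged.

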### 2.6. Recruitment

The sample will be recruited from patients admitted to the rehabilitation section of the hospital following cardiological screening. A nurse will contact them by telephone to invite them to an informative talk. During this meeting, patients will be informed about the importance of a healthy lifestyle, maintaining physical and mental health, and being active, as well as about the characteristics of the rehabilitation program itself and the tests that will be implemented. Patients will also be encouraged to attend the pre-test and post-test sessions and to attend at least 90% of the training sessions. Information will be provided by the rehab doctor, the physiotherapist, the nurse, and the physical exercise graduate. If the patients agree to participate, they then have to sign the written consent form.

### 2.7. Allocation and Blinding

A block randomization method will be used to allocate participants to the groups, which will contain equal sample sizes. Blocks will be chosen randomly by tossing a coin to determine participant assignment to the groups. This procedure will be carried out by the data monitoring committee. The participants and the data monitoring committee will be blinded to the group assignment exercise.

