This will be an 8-week, single-center, prospective, cluster-randomized controlled trial protocol in which post-stroke patients are assigned to either an HRV-based training group (HRV-G) or a HIIT training group (HIIT-G). A block randomization method will be used to randomly assign groups to interventions in equally sized sample groups. This protocol was designed in accordance with the Standard Protocol Items: Recommendations for Interventional Trials (SPIRIT) Statement [32]. To describe the intervention, the TIDieR (Template for Intervention Description and Replication) checklist by Hoffmann et al. (2014) [33] was used.

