### 2.3. Interventions

To implement this protocol, it will be necessary to include a physical exercise graduate in the multidisciplinary group (described in Section 2.1), who will design and conduct the intervention. This will ensure that patients are controlled, monitored, and directed by a specialist at all times, thus guaranteeing the safety of the protocol and optimizing the intervention.

The intervention program will be conducted over a period of 8 weeks, with three one-hour sessions/week. Every session will comprise a warmup, the main intervention, and a cooldown. The warmup and cooldown will last 10–12 min, respectively, and will be based on the dynamic mobilization of the main muscle groups, especially those of the lower body, to prepare and recover them, respectively, for the main part of the intervention. In the main part, lasting 30–35 min, aerobic-based exercise will be implemented. To reduce mechanical limitations while carrying out the exercise, both a treadmill and a cycloergometer will be used, rotating them weekly, as recommended by a recent meta-analysis [34]. Motivational strategies, such as playing music during the session and giving messages of encouragement, will be used by the professionals supervising the activity. The periodization of the intervention will include two training periods: a two-week familiarization period (FP) and a 6-week training period (TP). The FP will be common to both groups and will be used to increase the training intensity gradually to prepare the patients for the high-intensity TP. In the TP, each group will carry out the corresponding intervention. The HIIT-G group will train according to a predefined high-intensity training program. Taking into account that VO_2_ can be improved either with short or long HIIT intervals [9] and that patients are expected to be in poor physical condition, short training intervals of 1′30′′ will be combined with active rest periods. In each session, the work time at the determined intensity will be at least 50% of the total work interval. The training interval intensity will be gradually increased as the rest periods are reduced. In accordance with Taylor et al. (2017) [35], both the maximal heart rate and the subjective perception of effort will be controlled. The HIIT-G training periodization is presented in more detail in Table 1.

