The training prescribed to the HRV-G group will depend on the subjects’ daily HRV and will follow the HRV-training schema designed by Kiviniemi et al. (2007) [36] (Figure 1). The HRV registration procedure and analysis are described by Carrasco-Poyatos et al. (2020) [37], although, in accordance with the results from recent randomized controlled trials [38,39] and the characteristics of the sample, only high or low intensity will be considered for the present protocol.

The assigned study intervention will be modified or discontinued if the drug dose changes in response to harms, the participant requests it, the disease worsens, or the cardiologist recommends it. Compliance with the exercise protocol will be controlled by the nurse.

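### Section 2.7 claims blinding that the design does not provide, no outcome assessor is listed as blinded, and the coin-chosen blocks may be predictable to an extent the article leaves open

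*Protocol article*

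**What the plan says.** On allocation, section 2.7 states "Blocks will be chosen randomly by tossing a coin to determine participant assignment to the groups" and then "This procedure will be carried out by the data monitoring committee". The next sentence is the blinding statement: "The participants and the data monitoring committee will be blinded to the group assignment exercise". Nobody else is listed as blinded. Block size, the set of block patterns and the time at which an assignment is released are not given. Section 2.8 gives the same committee full access to the final dataset and does not mention coded arms.

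On what participants experience, section 2.3 says "The HIIT-G group will train according to a predefined high-intensity training program", set out session by session in Table 1, and "The training prescribed to the HRV-G group will depend on the subjects’ daily HRV". The Figure 1 legend adds that an HRV value below the normal range leads to low intensity or rest. Only the two-week familiarisation is common to both arms.

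On who measures, section 2.4 assigns the treadmill test, which yields the primary outcome, to the cardiologist. It also says: "Data on functional performance, relative weight and body fat distribution, quality of life, and cognitive function will be recorded by the multidisciplinary group". Section 2.3 places the exercise graduate who designs and conducts the training in that group. Section 2.4.8 has the group record adherence, feasibility and adverse events as well.

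On the unit of randomisation, the last paragraph of the Introduction says "A block randomization method will be used to randomly assign groups to interventions in equally sized sample groups", whereas section 2.7 speaks of participants.

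**The concern.** The blinding statement is wrong as written, not merely brief: two adjacent sentences conflict, and the interventions described elsewhere rule out participant blinding. An analysis plan could not repair this.

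The outcomes are of the kind that knowledge of the arm can move. VO2peak, the 6 min walk and the chair test depend on effort and encouragement. Quality of life is self-reported. Judging whether an adverse event relates to exercise involves discretion. The stated hypotheses favour HRV-guided training, including on safety and adherence. A reader told that participants and committee are blinded would underrate this risk.

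A separate, conditional risk is that an allocation built from coin-chosen blocks can be foreseen. If someone who recruits can foresee it, patients could be steered to an arm.

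**Working it through.** The plan states no figure on blinding or predictability to reproduce. It fixes only equal arms, 30 + 30 = 60 (section 2.5).

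**1. Committee.** Section 2.7 has the committee toss the coin that sets assignments, then calls it blinded to them. The two sentences agree only if the toss is for coded arms whose meaning another party holds. Neither section 2.7 nor section 2.8 says so.

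**2. Participants.** In weeks 1–2 both arms train alike. From week 3 the HIIT arm follows Table 1: intervals of 1′30″, rising from 85% to 95–100% of maximal heart rate. The HRV arm switches between high intensity and low intensity or rest according to the HRV reading. HRV appears to be recorded in everyone (section 2.4), so the measurement need not reveal the arm, but the prescription that follows from it does.

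**3. Assessors.** Setting section 2.4 beside section 2.7:
- treadmill test and blood samples: cardiologist, not listed as blinded;
- functional, body-composition, quality-of-life and cognitive measures: the group that includes the trainer, not listed as blinded;
- HRV, adherence, feasibility and safety: the exercise graduate (section 2.4) or the group (section 2.4.8), not listed as blinded.

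**4. Predictability.** The coin cannot be tossed freely per patient if arms must be equal: the chance of exactly 30/30 is C(60,30)/2^60 = 10.3%. So the coin must work through blocks. Assume individual assignment, a fixed block size b known to the observer, and visible past assignments. None of these is stated.

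- *Ordinary permuted blocks* (all balanced orders equally likely): an assignment is certain once one arm's b/2 places are filled. The expected share is 2/(b + 2). Check for b = 4: the six orders contain 2, 1, 1, 1, 1 and 2 certain places, and 8/24 = 1/3.
- *One toss choosing between two mirror-image blocks*: everything after the first place is certain, a share of (b − 1)/b.

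| b | Ordinary: certain share | of 60 | Mirror pair: certain share | of 60 |
|---|---|---|---|---|
| 2 | 50% | 30 | 50% | 30 |
| 4 | 33% | 20 | 75% | 45 |
| 6 | 25% | 15 | 83% | 50 |
| 10 | 17% | 10 | 90% | 54 |

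The accuracy of the best guess over all assignments, for b = 2, 4, 6 and 10, is 75%, 71%, 68% and 65% with ordinary blocks. With the mirror pair it is (b − 0.5)/b = 75%, 87.5%, 92% and 95%.

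**5. Unit.** If whole groups are assigned, as the Introduction says, the table does not apply as it stands.

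**The case against.** The strongest reply concerns allocation. The committee comes from the university (section 2.9) and the hospital team recruits (section 2.6), so allocating and recruiting are already separate. Nothing says that recruiters see the sequence, and a condensed article may leave concealment to the full protocol. This stands: steering by recruiters is not shown, and silence on concealment is not itself an error. It is why predictability is put here only as a conditional range.

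Four stronger readings are tempting and are not supported:

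- *A coin has two sides, so blocks are of two and half of all assignments are known in advance.* No block size, number of tosses or pattern set is stated. The share could be lower or higher than 50%, and the unit itself is unsettled.
- *The treadmill assessor is unmasked and is the only assessor who could be masked.* The article is silent on the cardiologist's masking. Laboratory staff, independent testers and the analyst could be masked too.
- *A committee blind to arm cannot judge harm by arm.* Review with coded arms permits the comparison.
- *The cardiologist can simply be masked.* Section 2.3 lets the cardiologist recommend modifying or stopping the assigned intervention, which makes masking that role doubtful as planned.

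It may also be said that participants could be kept unaware of the hypothesis or of the other arm's rule. That would be a weaker claim than blinding to assignment, and the article does not make it.

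**Conclusion.** The point holds in this form. Section 2.7 contradicts itself on the committee, and participant blinding is not achievable once the arms diverge. Both follow from the text without further assumptions, apart from the absence of a coded-arm procedure. No outcome assessor is listed as blinded, and training and measurement overlap for most secondary outcomes.

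The bias that could result cannot be computed from the article. Predictability is a possible addition: 17–50% of assignments certain with ordinary blocks of 10 down to 2, or 50–90% with two mirror-image blocks of 2 up to 10. These ranges rest on individual assignment, a known fixed block size and visible past assignments. If any of these fails, they do not apply.

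**What to change.** In section 2.7:

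(a) State that the trial is open-label for participants and trainers. Delete the claim that participants and the allocating committee are blinded.

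(b) First reconcile the unit of randomisation (groups in the Introduction, participants in section 2.7). Then replace the coin with a computer-generated list of permuted blocks of varying size. A university member outside both the committee and the recruiting team should hold it and release each assignment only after consent and baseline tests. The schedule leaves room for this, because the first-week tests fall within the familiarisation common to both arms.

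(c) Give the analyst and the committee data with coded arms. Keep the treadmill assessor unaware of arm where this is compatible with the cardiologist's role in section 2.3, and log any unmasking.

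The cost is protocol wording, a short program for the list and a coded dataset. Whether masked treadmill testing needs another person cannot be told from the article. Patients must be asked not to reveal their arm at the post-test, and the blinding statement becomes less favourable. The functional, quality-of-life and cognitive measures would still be recorded by the group that includes the trainer, and the text should say so.
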